***Vita Mamba* School Feeding Project**

**Study Protocol**

**Abstract**

This study builds on the *Mamba Lespri* School Feeding Project, conducted in Cap-Haitien, 2012-2013, to improve the nutrition of school-aged children, now in a rural context. Our main objective is to test the effect of a locally produced food, Vita Mamba, on reducing anemia and improving growth in school-aged children. The study uses a longitudinal randomized cluster design with three schools assigned to two groups : Group 1: Control (deworming), Group 2: Vita Mamba (and deworming). Schools will be matched on socio-economic, demographic, and nutritional characteristics and randomly assigned to one of the two comparison groups. Approximately 400 Haitian school children ages 3-16 years of age and their parents will be recruited and enrolled to be followed during the 2014-2015 school year. Data will be collected from two groups of participants at each school: children and parents. At baseline, socio-economic and demographic information will be collected from parents. Children will then be followed at two time points: at the beginning (baseline) and end (endline) of the study for nutrition measures (weight and height, and hemoglobin concentration). Parents will be surveyed for socio-economic characteristics, child diet and health, and anthropometry.

**Background and Significance.** The Haitian Ministry of Education has identified poor nutrition as a problem among Haitian school children. Poor nutrition stunts growth and development and compromises the immune system, leaving the body more vulnerable to disease. In Haiti, 20.9% of children less than five years are stunted and 11.4% are underweight (MSPP, 2013), but information about the nutritional status of the school-aged population is limited. One study of Haitian children between the ages of 11 and 19 years showed two-fifths were stunted (Psoter, et al, 2008).

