Before the launch of the pilot study, WUSTL will form the study team, which will review and complete the necessary IRB certification program appropriate for this project. The training will include three (3) components: 1) Technical information and survey administration; 2) protocol instruction for anthropometric and hemoglobin concentration measure; and 3) field testing and validation exercises. The team of enumerators will receive detailed information regarding the product’s ingredients, functionality, and recommended consumption rates. Additional training will be provided to the team to explain the consent process as well as data collection and communication methodologies. Instructions will be given to the team on the correct methodology for conducting the acceptability study.

Intervention Phase.

**Sample Schools and Participants.** The intervention phase of the project will take place during the academic year from September 2014 through June 2015. Selection of the three schools in a communal section of the Great Basin region (Northeast Department) will be based on student socio-economic and demographic information, school size, and current school feeding program. All schools and students have an equitable chance of being included in the study. Three (3) schools will then be matched on important characteristics (basic anthropometry, SES, and school size) and will be assigned to one of two study groups described above: Group 1: Control (Danda); Group 2: Vita Mamba (Dolval).

At each of the three schools, two groups of participants will be part of the study: parents and children. A full description of the study will be provided and they will be invited to participate through the informed consent process. Parents and other caregivers of potentially eligible children will also be contacted at the beginning of the school year. They will be provided with a description of the study and invited to attend one of several meetings at the school with their children. At the meeting, the Study Coordinator will review and provide a full description of the study.

Children of interested parents/caregivers will be screened for eligibility based on the following criteria:

• Children 3-16 years old ;

• Children in good health [no fever, no congenital health condition];

• Children not severely malnourished [weight-for-height Z score >-2];

• Enrollment in the study school for the academic year 2014-2015.

Exclusion criteria are the following:

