• Allergy to peanuts or soy;

• Fever or congenital or major health condition affecting the child;

• Child severely malnourished (weight-for-height Z score <-2).

Once eligibility is established, parents/caregivers will go through the informed consent process individually. The study staff will provide the children with a verbal description of the study, which will explain the purpose of the study, their role in the study and what to expect during the data collection methods. The children will be asked to give verbal assent. Following this, parents will be asked to return to the school on a scheduled date and the baseline survey will be administered.

**Sample size.** Power calculations were used to determine the adequacy of sample size, predetermined by total number of eligible children in the study schools and study budget. Using an estimate of difference-in-difference, mean change in Hb of 0.40 (SD 1.2) based on previous studies, adequate sample size need was estimated to be 143 per group [alpha=0.05 and power (1-β=0.80)] (Nga T. et al. 2009). With a design effect of 1.06 applied and an estimated 10% losses to follow-up, the study was found to be adequately powered to detect the hypothesized difference in Hb with 321 children enrolled (Wittes et al. 2002).

**Intervention & Methods.** Students in Group 2 will receive the RUSF/Vita Mamba snack daily for one academic year, 2014-2015. Each RUSF sachet (50g) contains 260 kcal and 100% RDA for most micronutrients. Simple messages about the importance of the RUSF, nutrition, and hygiene will be communicated at a low intensity level in group 2. All children will receive deworming, Albendazole, according to the national protocol of MSPP. Two types of surveys will be developed and administered for data collection in this study.

*Child measures and survey:* Students will be followed longitudinally during the school year on a range of health, nutrition, and education outcomes. A baseline, midline, and endline survey will be administered to assess nutrition and education impacts as well as acceptability of the product, Vita Mamba, to students as part of a school feeding program.

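### The enrolment of 321 does not carry both the 1.06 design effect and the 10% loss (the inputs give 334 to 337), rests on an unstated equal split, and is not reconciled with the 400 in the Abstract

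*Protocol*

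**What the plan says.** The Sample size paragraph (Protocol, Methodology) takes a "mean change in Hb of 0.40 (SD 1.2) based on previous studies" as the difference-in-difference to detect, with "alpha=0.05 and power (1-β=0.80". From these inputs, "adequate sample size need was estimated to be 143 per group". It then says that a design effect of 1.06 and an expected 10% loss were applied, and that the study is "adequately powered to detect the hypothesized difference in Hb with 321 children enrolled". The same paragraph says the sample was fixed in advance by the number of eligible children and the budget, so the calculation is a check of adequacy.

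The Abstract gives another enrolment figure: "Approximately 400 Haitian school children ages 3-16 years of age and their parents will be recruited and enrolled".

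On allocation, the Abstract and the Study Design paragraph put three schools into two groups. Sample Schools and Participants says "Three (3) schools will then be matched on important characteristics (basic anthropometry, SES, and school size". That paragraph then names one school for each group and does not place the third. No child-level ratio and no enrolment per school is given.

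**The concern.** The paragraph states every input and the result, so a reader can check the result, and it does not follow from the inputs. The claim of adequate power refers to 80%, and 321 is the only number to which the protocol attaches that claim.

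Two further points bear on it. A figure of 143 per group presupposes equal groups, whereas three schools of similar size in two groups would tend towards one third against two thirds, and an unequal split lowers power for the same total. Also, a second enrolment figure stands in the Abstract, and the choice matters: on the protocol's own inputs, power is a little or clearly below 80% at 321, depending on the split, and above 80% at 400.

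**Working it through.** **Inputs.** From the Sample size paragraph: difference 0.40, SD 1.2, alpha 0.05, power 0.80, 143 per group, design effect 1.06, loss 10%, enrolment 321. From the Abstract: about 400. Sidedness is not stated; two-sided is used because it reproduces 143 (one-sided gives 112).

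**Step 1: the base figure reproduces.**
n per group = 2 x (1.96 + 0.8416)² x 1.2² / 0.40² = 141.3, so 142. The t-based solution is 142.2, so 143. Both groups together: 2 x 143 = 286.

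**Step 2: the inflation does not.**
- Design effect: 286 x 1.06 = 303.2
- Loss by division: 303.2 / 0.90 = 336.8, so 337
- Loss by multiplication: 303.2 x 1.10 = 333.5, so 334
- From a base of 142: 335 or 332

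These are 11 to 16 children above 321. For comparison, loss alone gives 286 / 0.90 = 318, design effect alone gives 304, and 286 x 1.06 x 1.06 = 321.3. So 321 is near a single adjustment for loss, or 1.06 applied twice, but is not 1.06 together with 10%.

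**Step 3: what 321 covers.**
Loss covered with the 1.06 in place: 1 - 303.16 / 321 = 5.6%.
Effective number with 10% loss: 321 x 0.90 / 1.06 = 272.5, about 136 per group if equal.

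**Step 4: power.** With effective group sizes n1 and n2, the normal approximation is Φ(0.40 / (1.2 x √(1/n1 + 1/n2)) - 1.96). For equal groups at 321, n1 = n2 = 136.3: 0.40 / (1.2 x 0.1212) = 2.75, and Φ(0.79) = 78.6%. The t-based values are slightly lower. All rows use design effect 1.06 and 10% loss; the unequal splits are assumptions, shown as a range.

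| Enrolled | Split | Power (normal) | Power (t) |
|---|---|---|---|
| 321 | 1:1 | 78.6% | 78.3% |
| 321 | 45:55 | 78.2% | 77.9% |
| 321 | 40:60 | 76.9% | 76.6% |
| 321 | 1:2 | 73.7% | 73.4% |
| 337 | 1:1 | 80.5% | 80.2% |
| 400 | 1:1 | 86.7% | 86.5% |
| 400 | 1:2 | 82.5% | 82.3% |

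At an assumed 1:2 split, 80% power needs 106.6 children in the smaller group (t-based), so 3 x 106.6 x 1.06 / 0.90 = 377 enrolled.

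**The case against.** The strongest reply is that the slip is small. The shortfall against 337 is 16 children, or 5% of 321, and with equal groups power stays within 2 points of 80%. The sample was fixed by eligibility and budget, so the calculation does not drive recruitment, and the roughly 400 planned would be enough on the protocol's inputs even at 1:2. All of this stands and sets the severity. It does not make 321 follow from the stated inputs.

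Three stronger readings are tempting, and the documents do not support them.

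- A reader might infer that three size-matched schools make equal groups impossible. Matching on school size does not fix how many children enrol from each school, and the protocol gives no ratio and no group for the third school. An unequal split is likely; 1:2 is the far end of the range shown.
- A reader might compare the smaller group at 1:2, about 107 of 321, with 143 and call it short even before losses. But 143 is the need per group under 1:1 only. A split of 107 against 214 has 80.1% power before design effect and loss. The shortfall appears only once those two are applied.
- A reader might call 321 and 400 a contradiction. The first can be read as a number found sufficient and the second as the recruitment plan. The protocol does not say so and calls both enrolled, so they are unreconciled, which is a weaker fault.

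**Conclusion.** The enrolment of 321 is wrong as written: the protocol's own inputs give 337 (334 with the loss multiplied). With equal groups the cost is under 2 points of power, about 78% against the stated 80%. If the split is unequal the cost is larger, down to about 73% at an assumed 1:2. At about 400 enrolled, power is above 80% at both 1:1 and 1:2.

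These figures rest on a two-sided test and on the stated 10% loss. Above all they rest on the design effect of 1.06, which is taken as given here and not endorsed. Assuming three equal schools of 107 children, it implies an intraclass correlation of 0.06 / 106, about 0.0006. Every power figure above is conditional on that value.

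This is a modest correction of text and does not call for a change of design.

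**What to change.** In the Sample size paragraph, either replace 321 with about 337 or keep 321 and restate power as about 78% with equal groups under the stated design effect and loss.

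Say whether about 400 is the enrolment target and the other figure the minimum, and use one target in both the Abstract and the Sample size paragraph.

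In Sample Schools and Participants, state which group the third school joins and the expected split of children. Give power for that split, with a note that it is conditional on the design effect of 1.06.

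The cost is text only. If about 400 is the plan, no extra recruitment follows. If eligibility or budget caps enrolment at 321, the stated power drops by about 2 points with equal groups, and by more if the split is unequal.

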The diets of school-aged children are likely deficient in vitamin A, iron, iodine, zinc, and potentially other micronutrients, similar to younger children in Haiti (Best, et al, 2010). Among 4-5 year olds, 35% were found to be vitamin A deficient and almost half were anemic (WHO, 2007), which can affect cognitive development, memory, and other mental function (NIH, 2011). Iodine deficiency, which has been associated with lower IQ scores, affects 59% of the entire Haitian population (MSPP, 2005). The exact prevalence of zinc deficiency in Haiti is unknown as is the case for most countries given the difficulties in measuring zinc nutrition though diarrhea prevalence, which is associated with zinc deficiency, is high in Haiti (MSPP, 2007). Intestinal parasites closely linked to nutrient deficiencies infect about a third of all Haitian school-aged children (WFP, 2010). Inadequate calories, protein and micronutrients stunt growth and intellectual development and compromise the immune system, leaving the body more vulnerable to disease (WHO, 2000).

In Haiti, despite the numerous and longstanding school feeding projects, there is limited information about the health and educational outcomes of these programs. Few programs have conducted evaluations designed to demonstrate impact or even program performance.  This study is designed to first characterize the nutritional situation of school-age children, and second, evaluate the effectiveness of a Ready-to-Use Supplementary Food (RUSF), Vita Mamba, for nutrition, health, and educational outcomes. It is among the first globally to examine a lipid-based RUSF in school-age children. The project will be implemented in the north of Haiti, in the Terrier Rouge zone. Vita Mamba will be introduced as a snack targeting children 3-12 years of age within a school feeding program.

**Study Aims:** To evaluate the nutrition impacts, especially growth and reduction of anemia, associated with the local product (Vita Mamba) offered through school feeding programs.

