Hemoglobin concentrations in the students will be determined using the Hemocue system, which measures red blood cell status and is reported in grams per 100 milliliters (g/dl). A droplet of blood will be collected in a sterile fashion with a fingerstick and a microcuvette in one continuous process. The results will be compared to WHO anemia Hemoglobin cut-offs for children 5 - 11 years of age (WHO, 2011). The Seca Model 874 (Digital) 440 lb x 0.1 lb resolution and the ShorrBoard measuring board will be used to collect weight and height measures. These measures will be used to determine body mass index (BMI), anthropometric z-scores, and the prevalence of stunting, underweight and wasting, which will be compared to WHO Growth Standards.

*Parental survey:* At baseline and endline, a survey will be administered at the school to parents of children in the study. At baseline, after informed consent procedures, socio-economic and demographic information will be collected, including parental education, age, occupation, family size, income/assets, household water and sanitation services, health and nutrition behaviors, and access to healthcare. This will allow the evaluation team to control for confounding factors and stratify analyses. Further, additional recall data on frequency of consumption, dietary diversity, and morbidities of participating children will be collected from parents at both baseline and endline time points. Finally, height and weight measures will be taken on the parents.

Reporting & Dissemination Phase. During this phase, data will be analyzed and reports written based on the results of the study. Presentations will be made to donors, MSPP, PNCS, MFK, and the community with the results and next steps. Other dissemination activities could include writing policy and programming briefs and journal articles, and presenting at national and international conferences.

**Innovations and Impacts.** This is the first study to examine the effectiveness of a Ready-to-Use Supplementary Food (RUSF) with deworming in a rural Haitian context for addressing poor nutrition. If there are positive findings, the results may be used to increase and advance the school feeding programs in Haiti. Further, there is potential to affect policy and programming at the national level with regards to child nutrition in Haiti. At the international level, this study will contribute to the evidence base for supplementary foods as part of a school feeding protocol.

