Appendix C: Analysis

The primary outcomes tested by the study will be height, weight, and hemoglobin levels of the child, as markers of growth and micronutrient nutrition. The secondary outcomes include: nutrition (weight, diet, and dietary intake); health (morbidities such as diarrhea, and fever). Finally, the study will be examining the feasibility and acceptability of using Vita Mamba in the school feeding context and thus looking at ease of delivery.

The analysis methods will include descriptive and experimental data procedures. Several univariate analyses and multivariate regression analyses will be run to model outcomes and adjust for potential confounding factors. As a longitudinal study, the study will run panel regression by generalized least squared with random effects. Interaction terms will be introduced. As necessary, propensity score matching will be introduced to ensure the two groups are comparable.

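### The only anemia cut-off named is for ages 5-11, but children aged 3-16 are enrolled, so anemia status at 3-4 and 12-16 years rests on a cut-off meant for another age

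*Protocol*

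**What the plan says.** Under Intervention & Methods, in the paragraphs on child measures, the protocol describes the fingerstick hemoglobin test and then states: "The results will be compared to WHO anemia Hemoglobin cut-offs for children 5 - 11 years of age (WHO, 2011". No cut-off for any other age appears in the protocol, and no cut-off value is given.

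The enrolled range is wider. The Abstract says "Approximately 400 Haitian school children ages 3-16 years of age and their parents will be recruited", the eligibility list under Sample Schools and Participants says "Children 3-16 years old", and both group descriptions under Study Design use 3-16. Background and Significance gives a third range: "Vita Mamba will be introduced as a snack targeting children 3-12 years of age within a school feeding program".

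Anemia is part of the headline aim. The Abstract says "Our main objective is to test the effect of a locally produced food, Vita Mamba, on reducing anemia and improving growth", and the Study Aims say "To evaluate the nutrition impacts, especially growth and reduction of anemia". The outcome list in Appendix C is different in kind: "The primary outcomes tested by the study will be height, weight, and hemoglobin levels of the child". Anemia status or prevalence appears there neither as a primary nor as a secondary outcome. The sample size section also works on the continuous scale, with a "mean change in Hb of 0.40 (SD 1.2) based on previous studies".

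**The concern.** A cut-off labelled for ages 5-11 is age-specific by its own label. If it is applied to everyone, children of 3-4 and 12-16 years are classified by a threshold that the protocol does not claim for them. If it is applied only to ages 5-11, the other children have no anemia definition at all. Either way, the aim of reducing anemia lacks a sound definition for part of the enrolled population.

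This is not a detail that a protocol would ordinarily leave to a statistical analysis plan. The protocol fixes the comparator, and fixes it for a narrower population than it enrolls. An analysis plan that followed the sentence faithfully would carry the error forward.

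Two things are at stake. The first is the prevalence of anemia that the study reports to donors, ministries and the community. The second is the comparison between groups: three schools form two groups, so at least one group is a single school. The matching characteristics listed under Sample Schools and Participants (anthropometry, socio-economic status, school size) do not name child age, although the Abstract and Study Design refer to demographic factors more generally. If age mix differs between schools, the classification error does not fall equally on the two groups.

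**Working it through.** **1. How many eligible ages fall outside the cut-off's range**

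There is no protocol figure to reproduce on this point, so the first step is a count of single-year ages.

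- Enrolled 3-16: 16 − 3 + 1 = 14 ages. Inside 5-11: 7. Outside: 3, 4, 12, 13, 14, 15, 16 = 7. Share 7/14 = 50%.
- Under the 3-12 range in Background and Significance: 10 ages, of which 3, 4 and 12 are outside. Share 3/10 = 30%.

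These are shares of ages, not of children. The protocol gives no age distribution, and the sites are primary schools, so equal numbers at each age cannot be taken for granted.

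**2. Which analyses use the cut-off**

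The primary outcome in Appendix C is the hemoglobin level, and the sample size rests on mean change in hemoglobin. Neither uses a threshold. Only an anemia classification is affected.

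**3. Illustration of size**

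Inputs, assumed unless marked otherwise:

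- hemoglobin is normal with mean 12.0 g/dl at every age;
- SD 1.2: the figure is in the protocol, but attached there to the change in hemoglobin, so its use as the SD of a single measurement is an assumption;
- cut-offs 11.0 (ages 3-4), 11.5 (5-11) and 12.0 (12-16);
- equal numbers at each age and the same age mix in both groups;
- a gain of 0.40 g/dl (from the sample size section).

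Formula: prevalence = Φ((cut-off − mean)/SD).

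| Cut-off | Mean 12.0 | Mean 12.4 |
|---|---|---|
| 11.0 | Φ(−0.833) = 20.2% | Φ(−1.167) = 12.2% |
| 11.5 | Φ(−0.417) = 33.8% | Φ(−0.750) = 22.7% |
| 12.0 | Φ(0) = 50.0% | Φ(−0.333) = 36.9% |

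Overall prevalence, age-specific cut-offs, weights 2, 7 and 5 out of 14:

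- before: (2 × 20.2 + 7 × 33.8 + 5 × 50.0)/14 = 37.7%
- after: (2 × 12.2 + 7 × 22.7 + 5 × 36.9)/14 = 26.3%
- fall: 11.4 points

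Overall prevalence, single cut-off of 11.5:

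- before 33.8%, after 22.7%, fall 11.2 points (from unrounded values)

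The level is off by 3.8 points before rounding. The fall changes by about 0.2 points.

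**4. Range**

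Repeating step 3 with mean hemoglobin 11.5, 12.0 or 12.5 and neighbouring cut-offs 0.2 or 0.5 g/dl either side of 11.5:

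| Mean | Step | Single, level | Age-specific, level | Single, fall | Age-specific, fall |
|---|---|---|---|---|---|
| 11.5 | 0.2 | 50.0% | 51.4% | 13.1 | 13.1 |
| 11.5 | 0.5 | 50.0% | 53.5% | 13.1 | 12.7 |
| 12.0 | 0.2 | 33.8% | 35.3% | 11.2 | 11.4 |
| 12.0 | 0.5 | 33.8% | 37.7% | 11.2 | 11.4 |
| 12.5 | 0.2 | 20.2% | 21.4% | 8.1 | 8.4 |
| 12.5 | 0.5 | 20.2% | 23.7% | 8.1 | 8.7 |

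Over this range the overall level is off by 1.2 to 3.8 points, and the fall changes by less than 1 point.

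**5. If age mix differs between groups**

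Under the step 3 inputs, the error at ages 12-16 is 33.8 − 50.0 = −16.2 points, and at ages 5-11 it is zero. If one group had 10 percentage points more of its children at 12-16 in place of 5-11, the error in a cross-sectional group comparison would be 0.10 × 16.2 = 1.6 points. The 10 points are an assumption; the protocol documents no imbalance.

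**The case against.** The strongest reply is that no listed outcome depends on the cut-off. Appendix C tests hemoglobin levels, the sample size is built on them, and the sentence in question says only that results will be compared with cut-offs. In the same paragraph the word prevalence is used for stunting, underweight and wasting, not for anemia. This stands as a limit on the consequence. It does not remove the point, because reducing anemia is named in the Abstract and in the Study Aims, and that aim cannot be reported without a classification.

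A second reply is that one fixed cut-off applied to both groups at both time points produces errors that largely cancel in the comparison. This also stands where the age mix is similar, as steps 3 and 4 show. A third is that the protocol plans adjustment for confounders, stratification and, if needed, propensity score matching. This helps in part, but child age is not named as a covariate, and adjustment does not correct a reported prevalence.

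Three stronger readings are tempting, and the protocol does not support them. A reader might infer that anemia will be wrong for half of the children; the count is of single-year ages, and the share of children is unknown. A reader might set the 14 to 16 point error within the affected ages (33.8 − 20.2 = 13.6; 50.0 − 33.8 = 16.2) against the 11-point fall from a 0.40 g/dl gain and conclude that the error exceeds the treatment effect. The first is a level within a subgroup and the second a difference over all children, so they are not comparable. A reader might also infer that the trial's power or primary result is compromised; neither uses a cut-off.

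**Conclusion.** Wrong as written, but below the level of a must-fix. The protocol fixes an anemia comparator for ages 5-11 and enrolls ages 3-16, which leaves 7 of 14 eligible single-year ages (3 of 10 under the 3-12 range) outside it. The effect is confined to anemia classification.

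The true size and direction cannot be derived from the protocol. In the illustration, reported prevalence is off by about 1 to 4 points overall, and the treatment contrast moves by less than 1 point when both groups have the same age mix. That result rests on assumed cut-offs, an assumed mean that is the same at every age, an SD borrowed from the change in hemoglobin, and equal numbers at each age. Under the same assumptions, a 10-point imbalance in the share aged 12-16 would add about 1.6 points of error to a cross-sectional comparison. The main harm is to reported prevalence; harm to the group comparison depends mainly on an age imbalance that is possible with so few schools but is not shown.

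**What to change.** Replace the sentence on cut-offs with: *Anemia is defined by the cut-offs in the cited WHO 2011 document that apply to the child's age (and sex, where that source specifies it) at the date of each measurement.* Using age at each measurement settles the classification of children who pass from one age range to another during the school year.

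Include child age in any model of anemia, and report the age distribution by school so that a reader can judge comparability.

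Reconcile the 3-12 range in Background and Significance with the 3-16 range used elsewhere. Which range is intended is for the sponsor to state.

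The cost is one replaced sentence, one named covariate and one reconciled age range. No new measurement should be needed: age is required for eligibility, and the planned anthropometric z-scores imply that age and probably sex are recorded, although the protocol does not say so outright. The sponsor should confirm that both are on the data collection form.
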